### Methods/design

#### Aim and objectives

The aim of this mixed-methodology study is to evaluate the real world use of anticoagulation, in particular anti-FXa DOAC treatment (apixaban, edoxaban and rivaroxaban) in routine UK clinical practice in terms of patient characteristics, management pathways and patient-reported experiences of anticoagulation initiated following a first ischaemic stroke associated with non-valvular AF for patients who were not receiving anticoagulant therapy in the 12 months prior to the stroke.

The primary objective of this study is to describe the demographics, clinical characteristics and medical history of patients with AF presenting with a first ischaemic stroke who were not treated with anticoagulants in the 12 months prior to the stroke, according to the type of anticoagulant treatment subsequently prescribed for secondary stroke prevention (apixaban, edoxaban, rivaroxaban, warfarin, dabigatran, other anticoagulants or a documented decision not to initiate anticoagulation). Secondary study objectives will be evaluated only in patients treated with anti-FXa DOACs (apixaban, edoxaban, rivaroxaban), including describing the management pathways of patients initiated on anti-FXa DOAC treatment for secondary prevention of stroke; describing hospital resource use and the clinical assessments associated with anti-FXa DOAC treatment; describing patient-reported adherence to anti-FXa DOAC treatment; and describing patient-reported experience and satisfaction with anti-FXa DOAC treatment.

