### Study design and setting

This is a UK mixed methodology, non-interventional study, involving retrospective and prospective medical record reviews and a prospective patient survey, which is in progress in six UK National Health Service (NHS) secondary and tertiary care centres. Study centres have been selected to provide good geographic representation of centres experienced in prescribing apixaban, edoxaban and rivaroxaban for the secondary prevention of ischaemic stroke in patients with non-valvular AF. The key elements of study design are summarised in Fig. 1. The index event is the diagnosis of first ischaemic stroke associated with AF. The pre-index observation period is the 12-month period prior to the index event. The post-index observation period is the one month period following the index event. The post-DOAC observation period is the period from initiation of anti-FXa DOAC treatment up to a maximum of 7 months (6 months + 1 month window for completion of questionnaires) post-initiation.

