### Data sources and data collection

#### Retrospective medical record review

Data will be collected retrospectively from the hospital medical records of patients included in Group 1 in order to describe patient demographics and clinical characteristics and relevant medical history, including the components required to assess the CHA_2_DS_2_-VASc risk score (age, sex, history of congestive heart failure, hypertension, diabetes mellitus, stroke/transient ischaemic attack/thromboembolism, vascular disease). Where relevant, primary care data will also be requested from patients’ General Practitioners (GP). Data on the type of anticoagulant treatment prescribed for secondary prevention of stroke will be collected retrospectively for the one month post-index observation period. These time periods were chosen to ensure sufficient time to capture relevant data related to patient demographic and clinical characteristics prior to first stroke, accounting for variations in appointment timing and scheduling seen in routine clinical practice. A prior scoping exercise involving five healthcare professionals suggested that the data required to evaluate the primary endpoint (summary of CHA_2_DS_2_-VASc risk characteristics) are likely to be routinely recorded. Furthermore, the CHA_2_DS_2_-VASc risk score has been shown to be a useful predictor of patient outcomes over a 12 month period [15] and so a 12 month pre-index observation period was deemed appropriate. All data obtained from medical records will be recorded in electronic case report forms (eCRFs) designed specifically for the study, using a secure web-based electronic data capture system.

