### Prospective medical record review

Details of anti-FXa DOAC treatment and hospital resource utilisation will be sourced prospectively from the hospital medical records of patients included in Group 2 for the six-month period following initiation of anti-FXa DOAC treatment and entered into the eCRFs. In certain cases, it may be necessary to contact the patient’s GP to obtain information from primary care records. However, it is anticipated from feasibility assessments that important information about the patient’s treatment will be captured within the secondary care records, as it is likely that patients will be referred back into secondary care should any adjustment to their anticoagulant treatment be needed.

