### Study endpoints and variables

The primary endpoint of the study is the CHA_2_DS_2_-VASc Risk Score (scores range from 0 to 9) prior to initiation of anticoagulation for patients included in Group 1. Secondary endpoints to be evaluated in patients in Group 1 include patient demographics (including age, sex, body mass index [BMI], smoking status, alcohol use, ethnicity) and clinical characteristics (including time from AF diagnosis until stroke, recorded stroke severity, location of presentation with stroke [e.g. Emergency Department (ED), inpatient, outpatient, GP], and key clinical and laboratory evaluations at the time of stroke (including renal function, liver function and blood parameters), relevant medical history (including history of congestive heart failure, hypertension, diabetes mellitus, vascular disease [including myocardial infarction, aortic plaque, peripheral vascular disease], renal disease, hepatic disease), anticoagulant therapy initiated for secondary prevention of stroke, and relevant concomitant medication at the time of stroke and prescribed in the one month period after stroke. Secondary endpoints to be evaluated in patients in Group 2 include: the time between index event and date of anti-FXa DOAC initiation; anti-FXa DOACs and other anticoagulants prescribed during the post-DOAC observation period (including dose, and dosing frequency and reason for choice of first DOAC treatment, changes in dose and reasons for dose changes, DOAC discontinuation, time from initiation to discontinuation of first DOAC and reason(s) for discontinuation, anticoagulant treatments subsequently prescribed and reason(s) for choice/discontinuation); relevant medications newly prescribed in the post-DOAC observation period; clinical assessments (types and results of clinical assessments); hospital resource use (number, type [outpatient, inpatient, ED, other; planned or unplanned], setting [face-to-face, telephone, other], reason for hospital visits/consultations, length of stay for inpatient admissions, time to first follow-up visit from date of DOAC initiation) during the post-DOAC observation period.

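### Group 2 resource use and time to first follow-up run from DOAC initiation, which can precede discharge from the index stroke admission, so remaining stroke care may be mixed with later use

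*Protocol article*

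**What the plan says.** All references are to the protocol article.

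- **Objective.** Aim and objectives gives, as one secondary objective, "describing hospital resource use and the clinical assessments associated with anti-FXa DOAC treatment".
- **Window.** Study design and setting states: "The post-DOAC observation period is the period from initiation of anti-FXa DOAC treatment up to a maximum of 7 months". Prospective medical record review uses the same starting point: "hospital resource utilisation will be sourced prospectively from the hospital medical records of patients included in Group 2 for the six-month period following initiation".
- **Endpoint.** Study endpoints and variables lists the resource-use items, ending with "length of stay for inpatient admissions, time to first follow-up visit from date of DOAC initiation) during the post-DOAC observation period". Types and results of clinical assessments are a further Group 2 endpoint. The reason for each hospital contact is also collected, as is whether it was planned.
- **Index event.** Study design and setting: "The index event is the diagnosis of first ischaemic stroke associated with AF". This is a diagnosis date. No section uses discharge from the stroke admission as a boundary.
- **Timing of treatment start.** Retrospective medical record review: "Data on the type of anticoagulant treatment prescribed for secondary prevention of stroke will be collected retrospectively for the one month post-index observation period". The gap from stroke to treatment start is itself an endpoint ("the time between index event and date of anti-FXa DOAC initiation"), with no expected value given.
- **Hospital stay.** Limitations of the research methods refers to patients going home from hospital after their stroke, so at least some are admitted for the index event.

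**The concern.** The window is meant to capture hospital use that goes with DOAC treatment, but it opens on the day the drug is started, wherever the patient then is. Take two patients with the same stroke and the same length of stay. One starts the DOAC during the stay and the other after going home. The first can bring stroke-unit days and tests into the window; the second cannot. For the first patient, time to first follow-up also contains days when the patient was still in hospital for the stroke.

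At stake is the meaning of three Group 2 outputs: inpatient days, clinical assessments, and time to first follow-up. Subgroup and sensitivity analyses stratifies every Group 2 endpoint by first DOAC, and the Patients section expects centres to favour particular DOACs. Local habits on when to start could therefore shift the figures described for each stratum.

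**Working it through.** **No figure in the article bears on this point.** Its one precision calculation concerns the adherence score: 7.2 ± 1.96 × 1.2/√50 = 6.87 to 7.53, which agrees with the stated 6.9 to 7.5. The check below is therefore mainly one of text.

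**Step 1: can the window open before index discharge?** Prescribing is captured from the stroke diagnosis onwards, for one month. The centres are secondary and tertiary hospitals, and the article mentions discharge after stroke. No minimum gap between stroke and DOAC start is stated. So the window can open during the index admission. How often it does so is not given.

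**Step 2: what follows for each output?**

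- *Time to first follow-up visit.* The origin is explicit: DOAC initiation. If a follow-up visit means one after discharge, then for an inpatient starter: time from initiation = remaining index stay + time from discharge to visit. The first term enters by definition.
- *Clinical assessments.* Those made after DOAC start fall in the window by date, whether or not the patient is still in the stroke admission.
- *Inpatient days.* Two readings are open. If any inpatient day in the window counts, the remaining stroke stay is included. If only admissions that begin in the window count, it is not; but a patient still in the index stay cannot yet have a new admission, so time at risk differs by start timing.

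**Step 3: how large could it be?** Every input here is an assumption. Let L be the index length of stay, D the day of DOAC start, r = max(0, L − D) the stroke-stay days inside the window, and p the share of patients started as inpatients.

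- L = 7, D = 7: r = 0.
- L = 14, D = 4: r = 10. The mean per patient rises by p × r = 0.25 × 10 = 2.5 days at p = 25%, and by 10 days at p = 100%.
- L = 30, D = 1: r = 29.

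If all inpatient days in the window are counted, the index share of them is p·r/(p·r + b), where b is later readmission days per patient (readmission rate × stay):

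| r | b | p = 100% | p = 25% | p = 0 |
|---|---|---|---|---|
| 3 | 0.4 × 10 = 4 | 3/7 = 43% | 0.75/4.75 = 16% | 0% |
| 10 | 0.2 × 7 = 1.4 | 10/11.4 = 88% | 2.5/3.9 = 64% | 0% |
| 20 | 0.2 × 7 = 1.4 | 20/21.4 = 93% | 5/6.4 = 78% | 0% |

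The range runs from nil to most of the reported days, and the article does not narrow it.

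**The case against.** The strongest reply has four parts.

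1. *A counting rule for an admission already in progress belongs in the full protocol, the case report form or the SAP, none of which is shown.* This stands for inpatient days: the article's silence is not evidence that stroke-stay days will be counted. It does not stand for time to first follow-up, whose origin the article states outright, nor for the start of the window, which it states repeatedly.
2. *The collected items would let the index stay be separated.* Reason for visit, planned status and the stroke-to-DOAC interval would help. But no section says they will be used for this, and the index discharge date is not among the listed items.
3. *The study is descriptive.* Study sample size rules out formal comparisons between groups, and Limitations of the research methods disclaims causal inference and comparison of treatments. This limits the consequence for the strata. It does not settle what a single descriptive figure contains.
4. *Time from DOAC initiation is a legitimate quantity, and tests done in hospital after DOAC start may be the very assessments the objective wants described.* This stands. It is a reason to split the output rather than to move the origin or discard pre-discharge data.

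A reader might infer more than the text supports: that the rest of the stroke stay will certainly be reported as DOAC-related use, that acute care would dominate the figures, or that the objective cannot be met. The first treats one of two open readings as settled. The second needs a share of inpatient starters and lengths of stay that the article does not give. The third overlooks outpatient, emergency and telephone contacts and new admissions, which can still be described. Nor does the article say that patients are recruited at the moment of acute presentation; they are identified from department databases.

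**Conclusion.** The point holds as a weakness in a stated time origin. Both the window and time to first follow-up start at DOAC initiation, and that date can precede index discharge. For inpatient starters, time to first follow-up includes the remaining stroke stay, on the ordinary assumption that a follow-up visit comes after discharge. Inpatient days and clinical assessments may include acute stroke care, depending on a rule that the article does not give.

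The effect on the figures cannot be determined from the article. It is nil if all patients start after discharge, and could be large if many start early in a long stay. Confidence is high for time to first follow-up and moderate for inpatient days. The primary endpoint is untouched. This is a cheap improvement to secondary outputs and does not invalidate the study.

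**What to change.** Keep the window from DOAC initiation and make these changes to recording and reporting:

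- Record the date of discharge from the index stroke admission.
- Report index-admission days and clinical assessments after DOAC start on a separate line from use after discharge.
- Count as new admissions only those that begin after index discharge.
- Report time to first follow-up from DOAC initiation separately for patients started before and after discharge. For inpatient starters, add time from index discharge as a further variable, so that no single variable mixes two origins.
- Give the number started before and after discharge in every DOAC stratum.
- Express post-discharge use per patient-month, because inpatient starters have less post-discharge time in the window. Taking six months as 183 days, 10 remaining days leave 173 (5% less), and 29 leave 154 (16% less).
- When setting that denominator, reconcile the six-month record review ("for the six-month period following initiation of anti-FXa DOAC treatment") with the observation period of up to 7 months, whose extra month is there for questionnaires.

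The cost is one extra date, which the hospital records already under review should hold, and a few table lines. No change to sample size or follow-up is needed.

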**Fig. 1 Fig1:**
[figure not shown]
Study design and observation periods. **Group 1**: retrospective data collection for 300 eligible and consenting patients who present with first stroke associated with non-valvular atrial fibrillation (index event). The pre-index observation period is the 12-month period prior to the index event. The post-index observation period is the one month period following the index event **Group 2:** Prospective data collection for the first 150 eligible and consenting patients from Group 1 who commence treatment with apixaban (*n* = 50), edoxaban (*n* = 50), or rivaroxaban (*n* = 50). The post-DOAC observation period is from initiation of anti-FXa DOAC treatment up to a maximum of 7 months (6 months + 1 month window for completion of questionnaires) post-initiation. The baseline questionnaire will be completed within one month following anti-FXa DOAC initiation. The three-month questionnaire will be completed within the period beginning one week prior to and ending one month after the three-month post-initiation time point. The six-month questionnaire will be completed within the period beginning one week prior to and ending one month after the six-month post-initiation time point

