### Prospective patient survey

Patient-reported outcome data will be collected prospectively from patients in Group 2 via questionnaires administered at baseline (initiation of anti-FXa DOAC treatment + 1 month), and at 3 months (− 1 week/+ 1 month) and 6 months (− 1 week/+ 1 month) after initiation of anti-FXa DOAC treatment for secondary prevention of stroke. These time-points were chosen in order to allow an adequate amount of time between assessment points for DOAC treatment to take effect. Questionnaires will be administered face-to-face if patients are attending clinic at the relevant time point; they will be reminded of the study requirements and will be given the opportunity to decide whether or not they would still like to take part, prior to the questionnaire being administered. Otherwise questionnaires will be administered via telephone, which is a methodology for administration of patient questionnaires that has been used in prior studies, including a study relating to edoxaban treatment [16]. Where questionnaires are administered by telephone, the questionnaires will be posted to patients by members of their direct care team at the relevant time points to give patients an opportunity to contemplate their responses and complete the questionnaires in advance. Patients will be contacted by telephone to advise them that the questionnaire has been posted, to remind them of the study requirements and to ensure that they are still willing to participate in the study. A member of the direct care team or an external researcher will contact patients at an agreed date and time to collect their responses via telephone. The questions will be read to patients as written on the paper version and patients’ responses will be entered directly into the eCRF.

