Patient reported outcome measures include the Morisky Medication Adherence Scale (MMAS-8) questionnaire [17] and the Treatment Satisfaction Questionnaire for Medication (TSQM) questionnaire [18]. The MMAS-8 is a short, eight-item measure of treatment adherence that has previously been used to assess adherence to DOAC treatment in patients with venous thromboembolism [19]. The MMAS has been used widely in different diseases, populations and countries and has been administered face-to-face or via telephone [20–22]. The MMAS-8 is quicker to complete and has a higher degree of concordance with more objective measures of treatment (such as pharmacy fill data or electronic monitoring devices) than many other self-report measures [20]. In order to gain additional insight into recent levels of treatment adherence, patients will also be asked to report whether, how and how often they had taken their current anti-FXa DOAC treatment in the past seven days using a bespoke questionnaire. The TSQM is a widely validated general measure of treatment satisfaction which has been used for a variety of treatments and disease areas, including for measuring levels of patient satisfaction with anticoagulation treatment [23], and has been administered face-to face or via telephone [22]. The bespoke questionnaire will be administered to gain an understanding of the general experiences of patients with regard to other aspects of their care, such as communication, education about anti-FXa DOAC treatment and overall hospital experience.

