### Data analysis

Statistical analyses, including any data preparation prior to analysis, will be carried out using Stata v14 (StataCorp LLC) and Microsoft Excel (2010). Data from all centres will be pooled for analysis. Study endpoints will be presented as descriptive statistics of central tendency (median; arithmetic mean or geometric mean) and dispersion (interquartile range [IQR] and/or range; standard deviation [SD] and/or 95% confidence intervals [95% CI]) and/or frequencies and percentages, as appropriate for the type and distribution of the variables.

Total scores for the validated patient-reported questionnaires will be derived in accordance with published scoring algorithms for each measure [17, 18, 25]_._ Analyses will be conducted using only the results of those patients with data available.

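### Baseline adherence may be inflated by doses that hospital staff gave, because no listed variable or planned stratum separates these from doses the patient manages

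*Protocol article*

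**What the plan says.** Describing patient-reported adherence to the three anti-FXa DOACs is a secondary objective, evaluated in Group 2. Two instruments serve it. The first is described thus: "The MMAS-8 is a short, eight-item measure of treatment adherence". The second is a bespoke questionnaire, in which "patients will also be asked to report whether, how and how often they had taken their current anti-FXa DOAC treatment in the past seven days".

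On timing, the legend to Fig. 1 states: "The baseline questionnaire will be completed within one month following anti-FXa DOAC initiation". The same questionnaires follow, in the words of Prospective patient survey, "and at 3 months (− 1 week/+ 1 month) and 6 months (− 1 week/+ 1 month) after initiation of anti-FXa DOAC treatment". That section gives two routes of administration: "Questionnaires will be administered face-to-face if patients are attending clinic at the relevant time point" and "Otherwise questionnaires will be administered via telephone", the latter with a form posted beforehand.

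Under Patients, Group 2 entry depends on starting one of the three drugs and on being willing and able to complete the questionnaires. Discharge from hospital is not a condition. Among the resource-use variables is "length of stay for inpatient admissions", which is not linked to adherence.

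On who is analysed, Data analysis says: "Analyses will be conducted using only the results of those patients with data available". Subgroup and sensitivity analyses stratifies Group 2 endpoints by first DOAC, looks at patient-reported outcomes separately in patients who stay on their first drug and those who switch, and plans no sensitivity analysis. The limitations section names recall and reporting bias for self-reported adherence.

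**The concern.** Every Group 2 patient has just had a stroke, so the month in which the baseline form may be completed can overlap a hospital stay. While staff hand out the doses, an answer about what was taken describes the ward's drug round and not the patient's own habit. This is neither recall bias nor reporting bias. The patient may remember and report perfectly, and the answer still concerns something else, so the stated limitations do not cover it.

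The share of staff-given doses is likely to be largest soon after the stroke and smaller at 3 and 6 months, apart from readmissions and institutional care. The baseline mean may therefore sit above the level of self-managed adherence, and the three time points would then not measure quite the same thing. Adherence is a stated objective, and its mean score is the basis for the 50 patients per drug. A systematic shift of this kind does not shrink with sample size.

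**Working it through.** **1. The plan's own figure.** Inputs from Study sample size: n = 50 per drug, mean 7.2, SD 1.2, 95% limits.

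- Normal: 1.96 × 1.2/√50 = 0.333, giving 6.87 to 7.53.
- t with 49 degrees of freedom: half-width 0.341, giving 6.86 to 7.54.

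Both round to the stated 6.9 to 7.5. The precision statement is reproduced and is not in dispute.

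**2. Shift in the baseline mean (illustration).** The documents do not give the share f of patients who are staff-dosed at baseline, or their score. Assume that they score 8, taken as the top of the scale, and that all others average 7.2 at every visit.

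Baseline mean = 8f + 7.2(1 − f) = 7.2 + 0.8f, so the shift is 0.8f.

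| Staff-dosed share f | Baseline mean | Shift |
|---|---|---|
| 0% | 7.20 | 0.00 |
| 10% | 7.28 | 0.08 |
| 20% | 7.36 | 0.16 |
| 30% | 7.44 | 0.24 |
| 50% | 7.60 | 0.40 |
| 80% | 7.84 | 0.64 |

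The shift equals the planned half-width at f = 0.333/0.8, or about 42%. Below that share it is smaller than the sampling uncertainty the plan already accepts, but it runs in one direction.

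**3. Does a fall over time follow?** Not necessarily. Suppose self-managed adherence rises by 0.2 during follow-up and f = 20%. Baseline is then 7.36 and the later mean 7.40, a change of +0.04. With a rise of 0.4 and f = 50%, both means are 7.60 and the change is nil.

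**4. Reach of the seven-day item.** Assume the form is completed on a random day from 7 to 30 after initiation (24 possible days), and count the day of completion and the six days before it.

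- Discharge on day 10: forms on days 7 to 16 include at least one ward day, 10/24 = 42%.
- Discharge on day 20: forms on days 7 to 26 do, 20/24 = 83%.
- If only discharged patients answer, the affected days are 11 to 16 out of 11 to 30 (6/20 = 30%), or 21 to 26 out of 21 to 30 (6/10 = 60%).

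The discharge days are assumptions. These percentages apply to the seven-day item only and count periods with as little as one ward day. They cannot be used as f in step 2, because the article gives no recall period for the MMAS-8 and a patient with one ward day in seven is not wholly staff-dosed.

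**The case against.** The strongest reply is that the two routes of administration, clinic attendance and a telephone call after a posted form, both describe people living outside hospital, and that nothing says inpatients complete the questionnaire. This largely stands: answers given from a ward bed are an inference. It does not dispose of the point. Inpatients are not excluded either, and a patient telephoned within a week of discharge still reports on ward days.

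A reader might infer that adherence must then fall from baseline to 3 and 6 months by construction. The documents do not support that. A fall needs a material staff-dosed share, near-maximum scores in those patients and no offsetting rise in self-managed adherence, and none of these is given. No change-from-baseline adherence endpoint is stated either.

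A reader might also expect the by-drug tables to be distorted, since centres may favour particular drugs. Differences in length of stay between centres are speculation here. The article disclaims inference about how the drugs compare and allows centre enrolment targets.

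Three further points are fair. The sentence on available data is a rule about missing results, not a decision to merge care settings. The bespoke item asks how the drug was taken, and its wording, which is not shown, may capture some of this. Inpatient stays after initiation are collected, so overlap might be derived if dates are held. Even so, none of the stated strata uses that information. Finally, the exclusion of severe cognitive or emotive deficit should reduce carer and institutional dosing, though not dosing on a ward.

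**Conclusion.** The point holds as a possible upward bias at baseline. The article fixes the instruments, the window, the patients analysed and the strata, and followed as written these can mix staff-given with self-managed doses. Baseline and later adherence scores are therefore not clearly comparable.

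The direction rests on the reasonable assumption that staff-given doses are missed less often. The size cannot be derived from the documents. The illustrative shift is 0.8 times the staff-dosed share, resting on an assumed maximum of 8 and a mean of 7.2 in everyone else. It could be negligible if nearly all patients answer well after discharge. The planned sample size and its stated precision are unaffected.

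**What to change.** At each questionnaire, record two items: where the patient was during the recall period (hospital, institutional care or home), and whether the patient, a carer or staff gave the doses.

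In the analysis:

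- keep the overall adherence summary at each time point;
- report it again without staff-administered responses, and show those responses separately;
- describe the course over time in patients who were not staff-dosed at the time points shown;
- add staff-given dosing to the stated limitations.

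Carer-supported patients should stay in, because such support is part of the real-world use the study sets out to describe. The baseline questionnaire should not be delayed, because that could lose many responses.

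The cost is two extra eCRF items, one reporting rule and a smaller denominator, hence wider limits, for the baseline summary without staff-given doses.
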